### Estimation of sample size

Estimation of sample size was based on the distribution of the standardized beta-coefficients of the regression between accuracy and probability in the PC-based, contextualised Action Prediction task in children with typical development (M = 0.154, SD = 0.215) and with ASD (M = 0.008, SD = 0.112), with a between-group difference of moderate-to-large size (Cohen’s *d* = 0.87; see Amoruso et al., 2019 [45]). Given the difference in the standardised beta-coefficient between children with typical development and with ASD, an increase of moderate effect size in this outcome measure should represent a clinically relevant improvement in the ability to form predictive models of others’ behaviour, with a likely impact on social deficits and autism-like behaviours shown by patients with cerebellar malformations. Thus, we estimated that a moderate increase (0.13 mean change or 0.8 SD) of the standardised beta-coefficient after as compared to before the experimental training had clinical significance. Accordingly, a final sample of 21 patients per group has been set for our study in order to detect a between-group difference (independent sample *t t*est, two-tailed) between the effects of the experimental vs*.* control training (T2 − T0) of moderate effect size (Cohen’s *d* = 0.8) with a power of 0.80 and an alpha level set at 0.05. The software G Power 3 was used for this estimation.

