### Statistical methods

Demographic, clinical and neuropsychological variables of the two groups of patients are inspected through descriptive statistics. A *t* test and *χ*^2^ are used to assess the differences between the experimental and control training groups at baseline for continuous and categorical variables, respectively, thus allowing us to verify successful randomisation. For each outcome measure, we calculate the change between T0 and T2 (training effect delta) and between T0 and T3 (follow-up effect). Delta is calculated as the arithmetic difference between the second/third time points and the first time point. The delta values of the two groups for the primary outcome measure are compared using independent sample *t* tests (two-tailed). For the primary outcome measure, a Bonferroni correction procedure will be used to control for multiple comparisons. Multivariate analysis of variance will be used to explore differential effects of the trainings in the secondary outcome measures. As to what concerns missing data, a modified intention-to-treat analysis approach will be adopted, including in the analyses all the participants who had completed the pre- and post-treatment evaluation sessions, even if they had not completed all the training sessions. No imputation of missing data, however, will be used considering the limited sample size and observation points [58, 59]. The stratification factors (i.e. age and FSIQ), will not be considered in the statistical analyses, assuming that the stratification procedure has ensured a balanced distribution across the two groups.

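### The 0.80 power is not established for a 0.13 difference: d = 0.8 appears to rest on a single-occasion SD, while the planned test is on T2 − T0 changes

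*Protocol article*

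**What the plan says.** The sample-size section of the protocol article opens as follows: "Estimation of sample size was based on the distribution of the standardized beta-coefficients". These come from the computer-run Action Prediction task. The only distributions given are for "children with typical development (M = 0.154, SD = 0.215) and with ASD (M = 0.008, SD = 0.112"), each measured on one occasion, with a between-group d of 0.87. The section gives no SD of a change, no test–retest correlation and no SD for patients with cerebellar malformations.

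The target is then stated in two units at once, as a change within the experimental arm: "we estimated that a moderate increase (0.13 mean change or 0.8 SD) of the standardised beta-coefficient after as compared to before the experimental training". The next sentence carries the 0.8 over to the between-group contrast in T2 − T0, sized at 21 per group for a two-tailed independent t test, "with a power of 0.80 and an alpha level set at 0.05".

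Statistical methods fixes the analysis variable: "Delta is calculated as the arithmetic difference between the second/third time points and the first time point". The deltas of the two groups are compared by two-tailed independent t tests, without baseline adjustment.

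**The concern.** A t test on deltas is standardised by the SD of the delta. If the 0.8 was obtained by dividing 0.13 by a single-occasion SD, it is the d of that test only under a particular T0–T2 correlation, which the article neither states nor supports. The link between the raw difference that the article calls clinically relevant and the power it claims is then not established.

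The same sentences also move from a before–after change in one arm to a difference between arms. The two are the same only if the control arm does not change. Controls take the same task at T0 and T2, so their change is part of the contrast.

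This paragraph is the article's justification for 42 patients. A null result could be read as evidence against a 0.13 effect on the strength of a power figure that has not been shown to apply to that effect.

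**Working it through.** **Inputs from the protocol article.** Single-occasion SDs 0.215 (typical development) and 0.112 (ASD); means 0.154 and 0.008; target 0.13 = 0.8 SD; d = 0.8; 21 per group; two-tailed; alpha 0.05; power 0.80. **Assumed, because not given:** rho, the T0–T2 correlation of the beta-coefficient, over a range; equal SDs at T0 and T2 and in both arms.

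**1. The article's own sample size.** Noncentral t, two independent groups, d = 0.8, alpha 0.05:

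- Two-tailed: n = 25.5, so 26 per group. With 21 per group, power is 0.716.
- One-tailed: n = 20.03, so 21 per group, with power 0.817.

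The stated 21 per group is the one-tailed answer, although both sections specify a two-tailed test. This gap involves no SD and no rho.

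**2. Which SD lies behind the 0.8.** Implied SD = 0.13/0.8 = 0.1625. Candidates from the quoted figures:

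- mean of the two SDs: (0.215 + 0.112)/2 = 0.1635
- SD implied by the cited d: (0.154 − 0.008)/0.87 = 0.146/0.87 = 0.168
- root-mean-square of the two SDs: sqrt((0.215² + 0.112²)/2) = 0.171

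The first is nearly exact (0.8 × 0.1635 = 0.131). All three are single-occasion quantities.

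**3. SD of the tested variable.** SD(delta) = SD × sqrt(2(1 − rho)). Setting sqrt(2(1 − rho)) = 1 gives rho = 0.5, the only value at which the two SDs agree.

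**4. Power for a 0.13 difference in deltas**, SD 0.1625, 21 per group, two-sided alpha 0.05:

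| rho (assumed) | SD of delta | d = 0.13/SD of delta | power | n per group for 0.80 |
|---|---|---|---|---|
| 0 | 0.230 | 0.57 | 0.43 | 51 |
| 0.3 | 0.192 | 0.68 | 0.57 | 36 |
| 0.5 | 0.1625 | 0.80 | 0.72 | 26 |
| 0.6 | 0.145 | 0.89 | 0.81 | 21 |
| 0.7 | 0.126 | 1.03 | 0.90 | 16 |

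Power reaches 0.80 at rho of about 0.59. With the root-mean-square SD of 0.171, power is 0.40, 0.53, 0.67 and 0.87 at rho 0, 0.3, 0.5 and 0.7, and 0.80 is reached at about 0.63.

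**5. Separating the two causes.** At rho = 0.5 the choice of SD costs nothing, so the drop from 0.80 to 0.716 there comes wholly from step 1. The movement of power away from 0.716 as rho changes comes from the SD.

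**6. Baseline-adjusted alternative.** In an ANCOVA of the T2 beta on arm and T0 beta, the residual SD is SD × sqrt(1 − rho²), which never exceeds the single-occasion SD. With SD 0.1625 this is 0.1625, 0.155, 0.141 and 0.130 at rho 0, 0.3, 0.5 and 0.6. Then d is 0.80, 0.84, 0.92 and 1.00, and power is approximately 0.72, 0.76, 0.83 and 0.89 at 21 per group.

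**The case against.** The article never says which SD the 0.8 refers to. Its formal power input is a standardised d of 0.8 for the between-group difference in T2 − T0. On that reading the 0.80 is claimed for d = 0.8 and not for 0.13, and the paragraph contains an unstated assumption of rho = 0.5, not a miscalculation. The first half of this stands: the source of the SD is an inference from 0.13/0.8 = 0.1625 and from the absence of any other SD. The second half does not remove the point. The article itself presents 0.13 and 0.8 SD as the same quantity and derives the sample size from it, so the assumption carries the result and needs to be stated.

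A reader might go further and conclude that the trial is underpowered because rho must be low, reasoning from the sampling noise of a beta-coefficient fitted to one patient's trials. The document does not support this. It gives no trial number for the Action Prediction task, and if rho exceeds about 0.6 the power is above 0.80. A reader might also put figures on a retest gain in controls. No such figure is given, so only the definitional gap can be raised, not a size for it.

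It is also fair to say that a t test on change scores is valid in a randomised trial. ANCOVA is a gain in efficiency, not the repair of an invalid test.

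**Conclusion.** The point holds, without a fixed direction. The 0.80 power is not established for a 0.13 difference in T2 − T0 change. Over assumed rho from 0 to 0.7, the power at 21 per group runs from 0.43 to 0.90 and crosses 0.80 near rho 0.6. This rests on the inferred SD of 0.1625, equal SDs across occasions and arms, and transfer of SDs from other groups of children to these patients.

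One part does not depend on rho or on the SD: d = 0.8, two-tailed, alpha 0.05 and 21 per group give 0.716, not 0.80. That is a mismatch between one-tailed sizing and a two-tailed test and should not be attributed to the SD.

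The use of a within-arm change as a between-arm difference is a defect of definition whose size the document does not allow one to state.

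**What to change.** In Estimation of sample size:

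- State the SD assumed for T2 − T0, or the single-occasion SD together with rho and its source.
- Give the two-tailed power at 21 per group over a stated range of rho, as in the table above.
- Define 0.13 as the difference between arms in mean T2 − T0 change.

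In Statistical methods, analyse the T2 beta-coefficient by ANCOVA with the T0 beta-coefficient as covariate. The T0 value is already collected. At rho 0 and 0.3 this raises approximate power from 0.43 and 0.57 to 0.72 and 0.76, so 0.80 is still not reached at low rho, and the text should say so.

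The cost is a reworded paragraph with a less favourable stated power, and one extra model term.

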**Methods/design:**

The study is an interventional randomised controlled trial that aims to recruit 42 children, adolescents and young adults with congenital cerebellar malformations, randomly allocated to the experimental group or the active control group. The experimental group is administered the VR-Spirit, requiring the participants to compete with different avatars in the reaching of recreational equipment and implicitly prompting them to form expectations about their playing preference. The active control group participates in a VR-training with standard games currently adopted for motor rehabilitation. Both trainings are composed by eight 45-min sessions and are administered in the GRAIL VR laboratory (Motekforce Link, Netherlands), an integrated platform that allows patients to move in natural and attractive VR environments. An evaluation session in VR with the same paradigm used in the VR-Spirit but implemented in a different scenario is administered at the beginning (T0) of the two trainings (T1) and at the end (T2). Moreover, a battery of neurocognitive tests spanning different domains is administered to all participants at T0, T2 and in a follow-up session after 2 months from the end of the two trainings (T3).

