### Design

The study applies a single-centre, randomised, active-controlled trial design. Patients are allocated to one of two groups undergoing two different rehabilitation programmes through a stratified permuted block randomisation procedure [47]. Age and cognitive level (more recently available Full-scale Intelligent Quotient, FSIQ) are chosen as stratification factors. In particular, we consider two levels for age, corresponding to 7.0–12.9 and ≥ 13.0 years, and three stages for cognitive level consistent with, respectively, absence of intellectual disability (FSIQ > 80), from borderline intellectual functioning to mild intellectual disability (80 ≥ FSIQ ≥ 61) and from mild to moderate intellectual disability (60 ≥ FSIQ ≥ 45) (48). Doing so, six blocks are generated and within each block an estimated number of eight patients should be enrolled to achieve and overcome the established sample size. First, participants are allocated to a block depending on the two stratification variables. Second, patients are assigned to one of the two interventions according to specific permuted sequence. Details of the permuted blocks are reported in Table 1.

**Table 1 Tab1:** Stratified permuted blocks randomisation of the study

		Age	
		7–12.9 years	≥ 13.0 years
FSIQ	46–60	CCSSCCSS	SCSCSCSC
	61–80	SCCSSCCS	SSCCSSCC
	> 80	CSCSCSCS	CSSCCSSC

Legend: *FSIQ* Full-Scale Intelligent Quotient, *S* VR-Spirit training, *C* control training

Group 1 (S) receives the social prediction VR training for 2 weeks (four daily sessions in a week). In each 1-h session, 80 trials of the experimental programme and one of four motor games, selected among the applications available in the GRAIL, are administered; for each weekly session, a different game is administered in random order. Group 2 (C) receives a control VR training of the same duration (2 weeks, four 1-h sessions per week) as the experimental training; the control training involves, for each session, a navigational game and the daily repetition of all the four games from the GRAIL suite that are also presented, one per day, in the experimental session; the social prediction experimental programme is not presented in the control training.

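### The stated power of 0.80 is about 0.72 for 21 per group under the two-tailed test described, even with no losses, and the recruitment figures (42 and 48) are not reconciled with the analysed number

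*Protocol article*

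**What the plan says.** All references are to the protocol article.

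- **Estimation of sample size.** The effect treated as clinically relevant is "a moderate increase (0.13 mean change or 0.8 SD) of the standardised beta-coefficient". For the between-group comparison of T2 − T0 change, "a final sample of 21 patients per group has been set for our study", by a two-tailed independent-samples t test with d = 0.8, "with a power of 0.80 and an alpha level set at 0.05".
- **Abstract, Methods/design.** The trial "aims to recruit 42 children, adolescents and young adults with congenital cerebellar malformations".
- **Design.** Six strata are formed by age and FSIQ, and "within each block an estimated number of eight patients should be enrolled to achieve and overcome the established sample size". Table 1 prints eight allocations for each stratum.
- **Statistical methods.** The primary comparison is again a two-tailed independent-samples t test on the deltas. The analysis set is a modified intention-to-treat set, "including in the analyses all the participants who had completed the pre- and post-treatment evaluation sessions", whether or not all training sessions were completed. Missing data are not imputed.
- **Outcome measures.** The number of children who do not complete the training is counted as a feasibility measure. No expected rate is given.
- **Discussion.** The availability of patients may not allow every block to be filled.

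**The concern.** The printed power is tied to a specific number in the t test, 42. Two things looked wrong. First, the stated test, alpha and effect size do not appear to lead to 21 per group. Second, 42 is also the number to recruit, although the analysis set can only be equal to or smaller than the number randomised, while the Design section points to a different enrolment.

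If 0.80 stands, the team and readers will take 42 recruited as an adequately sized trial. The true chance of detecting the effect the protocol calls clinically relevant would be lower, and a non-significant result would be read as stronger evidence of no effect than it is.

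**Working it through.** **Inputs.** d = 0.8, two-tailed alpha 0.05, independent-samples t test, equal groups, 21 per group (Estimation of sample size). Recruitment is 42 (Abstract) or 6 × 8 = 48 (Design). The loss rate is not given, so 5, 10, 15 and 20% are assumptions.

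**Formula.** With n per group, degrees of freedom are 2n − 2, the noncentrality is δ = d·√(n/2), and power is the probability that a noncentral t with that δ falls beyond the two-tailed critical value.

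**Step 1: the plan's own figure.** For n = 21, δ = 0.8 × √10.5 = 2.592, df = 40, critical value 2.021. Power = 0.716, not 0.80.

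**Step 2: what 0.80 needs.** For n = 25, power is 0.791. For n = 26, δ = 0.8 × √13 = 2.884, df = 50, critical value 2.009, and power is 0.807. So 26 per group, 52 in total.

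**Step 3: where 21 could come from.** With a one-tailed alpha of 0.05 the critical value at df = 40 is 1.684 and power at n = 21 is 0.817; at n = 20 it is 0.799. So 21 is the smallest group size that reaches 0.80 in a one-tailed calculation. The d = 0.87 that the section quotes for the comparison of typical development and ASD does not explain it: the two-tailed power at n = 21 is then 0.785, and 22 per group are needed.

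**Step 4: loss from 42 recruited.** The middle column averages power over independent binomial losses in each arm of 21; the last gives a fixed equal split near the same total.

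| Assumed loss before T2 | Average power | Power at fixed n per group |
|---|---|---|
| 0% | 0.716 | 0.716 (21) |
| 5% | 0.691 | 0.693 (20) |
| 10% | 0.666 | 0.670 (19) |
| 15% | 0.638 | 0.645 (18) |
| 20% | 0.609 | 0.619 (17) |

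The chance that all 42 reach T2 is 0.95^42 = 0.116 at 5% loss and 0.90^42 = 0.012 at 10%.

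**Step 5: 48 enrolled.** The margin over 42 is 6/48 = 12.5%. The probability that at least 42 of 48 remain is 0.991, 0.800, 0.406 and 0.129 at 5, 10, 15 and 20% loss. If all 48 are analysed (24 per group), δ = 0.8 × √12 = 2.771, df = 46, and power is 0.774. With 10% loss, 43 analysed (21 and 22) give 0.726.

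**The case against.** The strongest reply is that the Design section already plans for more than the target. It separates the established sample size from a larger enrolment of about eight per stratum, so losses of up to 12.5% leave 42 analysed. That stands as far as keeping 42 is concerned. It does not rescue the stated power, since 42 analysed gives 0.72 and 48 gives 0.77. The margin is not described as an allowance for losses, the abstract does not carry it, and the Discussion doubts that the blocks will fill.

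Several stronger readings are tempting, and the article does not support them:

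- A reader might infer that the power statement holds as long as nobody is lost, so that attrition is the whole problem. It does not hold at zero loss; the drop from 0.80 to 0.72 has nothing to do with attrition.
- A reader might infer that the protocol expects dropouts. It only counts them, and it counts those who do not complete the training. Such a patient is still analysed if both evaluations were done. The interval from T0 to T2 is also short, with two weeks of training, so the higher loss rates are illustrations and not predictions.
- A reader might infer that a power claim for the T3 follow-up fails too. The trial is sized on T2 − T0 only, and no power is claimed at T3.
- A reader might infer from the match with 21 that a one-tailed test is intended. Both the sample-size and the analysis sections say two-tailed.

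A condensed article may leave the choice of a loss rate to the full protocol. That answers the missing rate. It does not answer a printed power that disagrees with its printed inputs, or two enrolment figures that differ.

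**Conclusion.** The point holds in this form. On its own inputs, the stated power of 0.80 is about 0.72 for 42 analysed patients, and 0.80 needs 52. If 42 is the number recruited, the exclusion of patients without T2 takes power to about 0.69 to 0.61 for assumed losses of 5 to 20%. If 48 are enrolled, power is at most 0.77.

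The figures without loss rest only on the article's test, alpha and d. The figures with loss rest on assumed rates and, where averaged, on losses that are independent and equal between arms. All use the full alpha of 0.05, as the sample-size section does; the Bonferroni correction planned for the primary outcome would lower power further and is not counted here. That 21 came from a one-tailed setting is a numerical match; the article does not say so.

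**What to change.** Make the Abstract, the Design section and the Estimation of sample size agree on one number randomised and one number analysed. Whichever enrolment figure is kept, replace the stated 0.80 with the two-tailed power at the expected analysed number: about 0.72 at 42 analysed, lower if 42 are randomised and some are lost, and at most 0.77 if 48 are randomised. State the loss rate assumed.

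Saying only that 48 are randomised so that 42 remain is not enough, because it would leave 0.80 in print for a design with about 0.72.

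The cost is rewording and a less favourable stated power. No patients beyond the 48 allocations already in Table 1 are required, and no separate power for T3.

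### With the stated inputs (two-tailed t test, d = 0.8, alpha 0.05), 21 patients per group give about 72% power, not 80%; 80% needs 26 per group

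*Protocol article*

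**What the plan says.** The section on estimation of sample size gives every input needed to check the number. It calls "a moderate increase (0.13 mean change or 0.8 SD) of the standardised beta-coefficient" clinically significant. It then states that "a final sample of 21 patients per group has been set for our study in order to detect a between-group difference" in the T2 − T0 change between experimental and control training. The test is an independent-samples t test, two-tailed, with Cohen's d = 0.8, "with a power of 0.80 and an alpha level set at 0.05". The software named is G Power 3.

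The section on statistical methods confirms the test: the group deltas for the primary outcome "are compared using independent sample *t* tests (two-tailed". It adds a Bonferroni correction for the primary outcome. It also says that age and FSIQ, the stratification factors, will not enter the analyses.

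On numbers enrolled, the Abstract says that the study "aims to recruit 42 children, adolescents and young adults with congenital cerebellar malformations". The Design section foresees about eight patients in each of six strata, so as to reach and exceed the established sample size, and Table 1 lists eight allocations per stratum.

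**The concern.** The number 21 looks too small for a two-tailed test at d = 0.8. If so, the trial does not have the power that it claims under the test that it plans. The stated chance of missing the target effect is 20%; the inputs imply about 28%, before any Bonferroni adjustment. A non-significant primary result would then be read as coming from an adequately powered trial when it did not. That matters in a population where, as the article itself warns, patients may be too few to fill all the strata.

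**Working it through.** **Inputs**, all from the sample-size section: d = 0.8, alpha = 0.05, target power 0.80, two-tailed, equal groups, n = 21 per group.

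**Method.** For two independent groups of n, the t statistic has df = 2n − 2 and noncentrality d × √(n/2). Power is the probability that this noncentral t falls beyond the critical value (beyond either critical value if two-tailed).

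**Step 1: the plan's own figure.** At n = 21, df = 40, noncentrality = 0.8 × √10.5 = 2.592, and the two-tailed critical value is 2.021. Power = **0.716**, so the stated 0.80 is not reproduced. The normal approximation gives 0.736, so the choice of algorithm does not explain the gap.

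**Step 2: the n that the inputs need.**

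| n per group | Two-tailed power | One-tailed power |
|---|---|---|
| 20 | 0.693 | 0.799 |
| 21 | 0.716 | 0.817 |
| 24 | 0.774 | 0.861 |
| 25 | 0.791 | 0.874 |
| 26 | 0.807 | 0.885 |

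Two-tailed, 80% is first reached at 26 per group, or 52 in total: 10 patients more than 42. One-tailed (critical value 1.684 at df = 40), it is first reached at exactly 21.

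**Step 3: the effect detectable with 21 per group.** Solving for two-tailed power of 0.80 gives d = 0.886, about 0.89.

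**Step 4: other readings that might give 21.**
- d = 0.87, which the section quotes for the difference between typically developing children and children with ASD: exact two-tailed power at 21 is 0.785, and 22 per group are needed. The normal approximation does give 21, but the plan states d = 0.8.
- Enrolment of 6 × 8 = 48, that is 24 per group: power 0.774.
- Covariate adjustment: none is planned.

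**Step 5: effect of the planned Bonferroni correction.** The calculation uses alpha 0.05. The primary outcome lists VR evaluation performance (T0, T2) and the Action Prediction coefficient (T0, T2, T3). This suggests two comparisons at T2, or three if the T3 change is counted. The article does not give the number, so this is an assumption. At n = 21 and d = 0.8, two-tailed:
- two comparisons, alpha = 0.05/2 = 0.025: power 0.606
- three comparisons, alpha = 0.05/3 = 0.0167: power 0.542

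**The case against.** The arithmetic itself is hard to dispute: the article states all the inputs and repeats the two-tailed test in its statistical methods. The fair objections concern what a reader might add to it.

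- **That a one-tailed setting was used.** The exact match at 21 invites this. The article does not show the software settings, and a two-tailed normal approximation at d = 0.87 also gives 21. The discrepancy is established; its cause is not.
- **That 42 is both the number recruited and the number needed, with no margin.** The Abstract alone suggests this. The Design section, however, foresees 48 allocations to exceed the target, and the sample-size section calls 21 per group a final sample. The Discussion warns that strata may not fill, so the 48 are not assured. The documents still do not support saying that no margin was foreseen.
- **That power is lower still because the 0.8 SD comes from cross-sectional SDs while the test uses change scores.** This depends on a T0–T2 correlation that the article does not give, and it can go either way. Take an SD of 0.168, which is (0.154 − 0.008)/0.87, and an SD of change of 0.168 × √(2(1 − r)). A change of 0.13 then has power 0.54 at r = 0.3, 0.69 at r = 0.5 and about 0.885 at r = 0.7. The plan states d = 0.8 directly for the between-group difference in change, so the check above needs no correlation.

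One objection stands in part: replacing 0.80 by 0.72 alone would still overstate the power of the primary analysis, because 0.72 is at unadjusted alpha. The restated figure must say so.

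**Conclusion.** The statement is wrong as written. At the stated d, alpha and sidedness, power with 21 per group is about 0.72, and 80% needs 26 per group. This rests only on the article's own figures and the standard equal-variance t test. Neither the planned enrolment of 48 nor the quoted d of 0.87 restores 0.80. The lower figures of about 0.61 and 0.54 after Bonferroni hold only if the number of primary comparisons is two or three. The finding does not make the two-tailed t test itself invalid; it corrects the power claimed for it.

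**What to change.** Keep 42 patients and the two-tailed test, and replace the power statement with wording such as:

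> With 21 analysed patients per group, power is 0.72 for d = 0.8 (0.80 for d = 0.89) at two-tailed alpha 0.05, before the Bonferroni correction.

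Then state how many primary comparisons the Bonferroni correction covers, and give the power at that alpha (about 0.61 at 0.025 for two comparisons, about 0.54 at 0.0167 for three). Do not make the test one-tailed to recover the 80%.

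The cost is one paragraph and a less favourable stated power. No patients are added and the test does not change. The article reports recruitment as still open, so the correction can be made before the final analysis.
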